## Abstract

**Abstract:**

**Introduction:**

The incidence of gestational diabetes mellitus (GDM) in Australia has tripled in the last 20 years. Consequently, over 40 000 pregnancies are now diagnosed as ‘higher risk’ each year. This has increased antenatal surveillance and obstetric intervention, often in the form of delivery earlier than 39 weeks gestation. The StUdy of Gestational diabetes And Risk using Electronic Data (SUGARED) project aims to use large population-based and routinely collected linked health data to (1) personalise risk prediction of adverse pregnancy outcomes for women undergoing glucose tolerance testing, (2) guide optimal birth timing for women with diet-controlled GDM and (3) examine variation in GDM management and pregnancy outcomes in New South Wales (NSW), Australia.

**Methods and analysis:**

This retrospective cohort study using linked, routinely collected health data includes all women who gave birth from January 2016 to December 2020 in NSW. The cohort will include approximately 475 000 pregnancies, with >70 000 diagnosed with GDM. The study will link birth data to hospital data and birth/death registry data. In addition, clinical pathology results and detailed clinical information from a subset of public hospital pregnancies in 13 of 15 area health services will be linked. To address the three main aims, we will use statistical methods including logistic regression and K-fold cross-validation for risk prediction, a propensity-score matching ‘target trial’ method to examine birth timing, and multilevel modelling to examine hospital variation.

**Ethics and dissemination:**

Ethics approval for the study has been granted by the NSW Population and Health Services Research Ethics Committee. We will communicate evidence generated from SUGARED to the local health districts and their clinicians, as well as potentially optimising dissemination using existing digital infrastructure.

STRENGTHS AND LIMITATIONS OF THIS STUDYThe StUdy of Gestational diabetes And Risk using Electronic Data project will use a large population-based cohort of pregnant women with and without gestational diabetes mellitus (GDM), providing a large sample size to investigate evidence gaps in the diagnosis, treatment and management of GDM in pregnancy.In novel data linkage, detailed clinical and pathology fields will be linked with the routinely collected perinatal and hospital data so that analyses can include such measures as glucose tolerance tests and whether the GDM is treated with diet or medication.A K-fold approach will be used to derive and validate risk prediction models, identifying subgroups of women with GDM who are at higher or lower risk of adverse outcomes.A ‘target trial emulation’ approach to determine the optimal timing of birth for women with GDM will be used, comparing pregnancies with planned delivery versus expectant management.The main limitation of this study is the observational nature of the data, meaning that the pregnancies and their outcomes are observed under normal treatment, and therefore, the ability to determine causal associations will be difficult. However, there is variation in diagnosis, treatment and management of GDM pregnancies across the New South Wales treatment centres, and this variation can be used to assess differences in the natural ‘treatment’ and ‘comparison’ groups.

## Introduction

 Gestational diabetes mellitus (GDM) is defined as glucose intolerance first diagnosed in pregnancy. Women with GDM are at increased risk of short-term pregnancy complications, obstetric interventions^1^ and longer-term development of type 2 diabetes and cardiovascular disease.^2^ Children of mothers with GDM face increased risk of preterm birth, higher birth weights, admission to neonatal intensive care, hypoglycaemia, respiratory distress^1^ and adverse health outcomes as adults.^2^ Australian women with GDM are often moved into a ‘higher risk’ care model, with more appointments, monitoring and testing than other pregnant women. They are recommended to adhere to lifestyle advice, undergo frequent blood glucose monitoring and, in some cases, require medication and undergo obstetric intervention such as labour induction.^3^

GDM incidence in Australia has tripled from 5.2% in 2000*–*2001 to 16.1% in 2017*–*2018,^4^ partly due to changes in maternal age, obesity and ethnicity but mostly due to altered diagnostic criteria identifying a greater proportion of women with GDM.^5^,^7^ Over 40 000 pregnancies are now classified annually as ‘higher risk’ in Australia, increasing antenatal surveillance and obstetric intervention, often in the form of delivery earlier than 39 weeks gestation. Though some women with severe or poorly controlled GDM have higher perinatal risks,^8^ many women require minor lifestyle changes, if any, and have very good perinatal outcomes. We posit that a universal set of GDM diagnostic criteria and management plan unnecessarily raises the obstetric intervention rate and cost burden on the healthcare system.^9^

The previous Australian diagnostic criteria were based on predicting type 2 diabetes risk after pregnancy.^10^ It was a two-step process, in which all pregnant women undertook a non-fasted glucose challenge test, with only those reaching a blood glucose threshold completing a subsequent 75 g oral glucose tolerance test (OGTT). The 2008 Hyperglycaemia and Adverse Pregnancy Outcomes study found evidence of a continuous relationship between maternal glucose levels and adverse outcomes in women with blood glucose levels below those diagnostic of GDM at the time.^5^ Those results led to new diagnostic criteria, endorsed by the International Association of Diabetes and Pregnancy Study Groups (IADPSG) in 2010, the WHO and Australasian Diabetes in Pregnancy Society in 2013, and recommended for adoption by the Royal Australia and New Zealand College of Obstetricians and Gynaecologists from January 2015.^11^,^13^ The new criteria used new glucose diagnostic cut-offs (fasting plasma glucose≥5.1 mmol/L, 1-hour plasma glucose≥10 mmol/L and 2-hour plasma glucose≥8.5 mmol/L^11^) and changed the diagnosis of GDM to a one-step universal fasted 75 g OGTT.

Single-centre observational studies in Australia have found no evidence of improved maternal or neonatal outcomes after the diagnostic change but noted increased GDM incidence^14^ and hospital costs.^15^ Even more compelling, a clinical trial comparing two-step Carpenter-Coustan screening (recommended by the American College of Obstetricians and Gynecologists (ACOG) and similar to the previous Australian two-step approach) with the revised IADPSG one-step approach found a difference in the proportion of women diagnosed (two-step: 8.5%, one-step: 16.5%) but unchanged perinatal and maternal complication risks. Similarly, the Gestational Diabetes Mellitus Trial of Diagnostic Detection Thresholds (GEMS) trial found a large difference in the proportion of women identified as having GDM (6.1% vs 15.3%) but a negligible difference in the proportion in each group with large-for-gestational age babies in women diagnosed and treated by either stringent or more relaxed GDM diagnostic criteria.^16^

Due to scarce and somewhat conflicting data, there are varying Australian and international recommendations for birth timing in women with GDM. The UK National Institute for Health and Care Excellence (NICE) guidelines recommend women with GDM and no complications deliver by 40^+6^, but that earlier birth be considered for women with GDM and other complications.^17^ The ACOG recommends that delivery in women with diet-controlled GDM should not be <39 weeks, unless otherwise indicated, and there should be expectant management up to 40^+6^ weeks.^18^ Within Australia, Queensland and South Australian guidelines recommend that women with well-managed, diet-controlled GDM await spontaneous labour.^19 20^ While many guidelines recommend expectant management, unless there are relevant clinical factors favouring early delivery, there is little consensus regarding the relevant clinical factors that should favour delivery before 39 weeks between states and centres and include a combination of macrosomia, foetal growth patterns, polyhydramnios, oligohydramnios, glycaemic control, maternal obstetric history, high body mass index (BMI), parity, cervical status and/or the woman’s preference. With the increase in number of women diagnosed with GDM, there is concern over a subsequent increase in early planned births and obstetric intervention.

A wealth of prospectively recorded data, generated through routine hospital care, can be linked at a population level and can deliver insights and guide clinical decision-making about antenatal management and timing of birth. Compared with a randomised controlled trial, using routinely collected clinical data has the advantage of examining patients in routine clinical practice, and significant variation in clinical practice across clinicians and hospitals can be used to assess outcomes. Through innovative use of routinely collected data and leading statistical methods, the StUdy of Gestational diabetes And Risk using Electronic Data (SUGARED) project objectives are to devise a more personalised risk prediction for the thousands of women with GDM, address the gap in evidence around birth timing for GDM pregnancies and examine variation in the management of and outcomes for GDM pregnancies. SUGARED will be conducted in New South Wales (NSW), Australia, using existing health data linkage infrastructure to create a population-level cohort of pregnancies to which we will link hospital, emergency, clinical maternity, pathology and vital status data.

To address the existing evidence gaps in the diagnosis and management of GDM, the SUGARED project aims to:

Identify subgroups of women with GDM with higher and lower risk of adverse outcomes.Among women with diet-controlled GDM, provide a gestational age-specific risk of neonatal morbidity and perinatal mortality associated with planned birth (induction of labour or no-labour caesarean section) compared with expectant management at term (≥37 weeks).Identify state-wide hospital variation in GDM-related risk, treatment and outcomes, including contributing individual and hospital-level factors, and the impact of the treatment variation on outcomes for women with GDM.

The results of aim 1 will enable obstetricians to better target obstetric surveillance and intervention(s). Aim 2 findings will provide guidance on the optimal timing of birth for women with GDM. The results from aim 3 will provide an understanding of the hospital variation in obstetric management for women with GDM and how this variation influences maternal and neonatal outcomes. This can then be used to facilitate a reduction in variation regardless of area of residence, leading to optimal outcomes for women with GDM.

## Methods and analysis

### Study design and population

This is a retrospective cohort study using linked routinely collected health data. All women who gave birth in NSW from January 2016 to December 2020 are included. The cohort will comprise approximately 475 000 pregnancies, with >70 000 diagnosed with GDM.

### Data sources

The NSW Perinatal Data Collection (PDC) will form the base of our cohort and be linked with other datasets, as shown in figure 1.

**Figure 1 F1:**
[figure not shown]
Population-based linkage of maternal antenatal, birth and postnatal data, including hospital, perinatal, pathology and deaths, and linked infant perinatal, hospital, pathology and death data. APDC, Admitted Patient Data Collection; EDDC, Emergency Department Data Collection; NSW, New South Wales; PDC, Perinatal Data Collection; RBDM, Register of Births, Deaths and Marriages.

The PDC is a statutory collection and primary source of information about pregnancy and outcomes for private, public and home births in NSW (≥20 weeks gestation or ≥400 g birth weight). It includes data on maternal demographics, pregnancy, delivery (mode and indication) and outcomes, such as gestational age and birth weight. Births from January 2016 to December 2020 will form the study population, and linked births from January 2001 to December 2015 will contribute previous birth information for cohort mothers. The NSW Register of Births, Deaths and Marriages (RBDM) is another statutory data collection that enumerates births. The RBDM birth data (July 2001 to December 2021) will provide additional demographic information for both parents and linked births, and the RBDM death data (January 2016 to December 2021) will provide linked death information for cohort mothers and babies.

The NSW Admitted Patient Data Collection (APDC) is a census of all inpatient hospital discharges. It will provide linked records for mothers and infants. It has demographic, clinical and health service information for each hospital separation. Up to 55 diagnoses and procedures are recorded for each hospital admission and coded according to the International Statistical Classification of Diseases (ICD) and Related Health Problems, Tenth Revision, Australian Modification and the Australian Classification of Health Interventions. Cohort mothers will have linked inpatient hospital episodes from July 2001 to December 2021 to provide lookback information about chronic conditions, previous procedures and health service usage, as well as antenatal and postnatal conditions and outcomes. Cohort babies will have linked inpatient episodes from January 2016 to December 2021 to provide information on neonatal morbidity and procedures, as well as any readmissions in the first year of life.

The NSW Emergency Department Data Collection (EDDC) collates patient presentations to the emergency departments (EDs) of public hospitals and in-scope contracted private hospitals in NSW, including presentations to 184 hospitals in NSW from 2016 to 2017. It includes data on patient demographics, triage category and diagnosis coded to ICD or Systemized Nomenclature of Medicine, Clinical Terms. All ED presentations from January 2005 to December 2021 will be linked with the cohort mothers, and ED presentations from January 2016 to December 2021 will be linked with the cohort babies to provide information on presentations, conditions and health service usage.

The NSW Pathology Data contains pathology test results from NSW public pathology facilities. Relevant pathology test results for the cohort mothers and babies from January 2016 to December 2020 will be linked to the cohort to get more information detail on OGTT results for the mother and blood glucose results for the mother and baby after the birth.

The eMaternity/ObstetriX data system (clinical maternity data) holds information about pregnancy and births in public hospitals in 13 out of 15 NSW local health districts (LHDs). During the study period, these LHDs transitioned from ObstetriX to eMaternity. There was a 6-month system overlap in each LHD, but all were using eMaternity alone by the end of 2017. A minimum dataset from eMaternity/ObstetriX is sent to NSW Health, collated into the PDC, along with the same information from private hospitals, the remaining public hospitals and some independent midwives. The clinical maternity data will be linked with the cohort for a small number of additional variables not in the PDC, but important for the understanding of variation in risk, diagnosis, severity and management of GDM, such as family history of diabetes and type of diabetes therapy during pregnancy. This more detailed maternity data will be linked with the population-level data from January 2016 to December 2020. The estimated NSW birth population coverage linked with each of the additional datasets is shown in figure 2.

**Figure 2 F2:**
[figure not shown]
Estimated NSW birth population coverage with the different linked datasets. *NSW Pathology contains only pathology tests done in public hospital pathology laboratories. †Emergency admission (EDDC) covers most public ED patients, but not the entire NSW population. Source: NSW Mothers and Babies Report, 2018. APDC, Admitted Patient Data Collection; EDDC, Emergency Department Data Collection; NSW, New South Wales; PDC, Perinatal Data Collection; RBDM, Register of Births, Deaths and Marriages.

### Data linkage

All record linkage will be conducted by the NSW Centre for Health Record Linkage (CHeReL)^21^ in accordance with NSW privacy guidelines. Probabilistic matching methods will be used to link individuals, incorporating name, date of birth, sex and address information, via ChoiceMaker software. The CHeReL uses the best-practice separation principle, wherein identifying information from each dataset is separated from clinical content data before linkage.^22^ Once linked, each record is assigned a unique person-number, with linkage keys identifying mother and baby pairs. Unique person-numbers are then attached to clinical data by data custodians, and deidentified health data are provided to researchers who merge datasets using the person-number. CHeReL record linkage validity is extremely high, with <1% of records having incorrect matches.^23^

### Defining gestational and pre-existing diabetes

The population with and without diabetes will be defined from the PDC and APDC. From 2016, the PDC revised diabetes capture, distinguishing pre-existing type 1 and type 2 and GDM. The APDC captures diabetes type in the antenatal period (if admitted) or in the birth record. Lookback information for the PDC and APDC will be used to identify women recorded as having GDM, but with pre-existing diabetes recorded in hospital or previous birth records. A previous validation study examining the reporting of diabetes in pregnancy in the PDC and APDC found better recording in hospital data, and as such, both linked datasets will be used to define the diabetes and diabetes type.^24^ Degree of glucose tolerance will be defined using OGTT results from Pathology and clinical maternity data. Whether the diabetes was diet or medication-controlled is recorded in the clinical maternity data.

### Outcome variables

Outcome measures will include as follows:

Obstetric interventions.Caesarean section.Induction.Caesarean or induction<39 weeks gestation.Instrumental birth.Episiotomy.Maternal outcomes.Maternal morbidity (validated composite indicator).Pregnancy hypertension.Pre-eclampsia.Postpartum haemorrhage.Perineal tears.Blood transfusion and number of blood packs used.Blood glucose at 6 months after birth.Length of hospital stay.Infant outcomes.Preterm birth (spontaneous).Stillbirth.Neonatal death.Perinatal mortality.Neonatal morbidity (validated composite indicator).Apgar at 5 min.Birth weight.Large for gestational age.Small for gestational age.Baby’s length.Shoulder dystocia.Bone fracture.Arm/hand palsy related to birth injury.Neonatal cord-blood pH.Transfer to neonatal intensive care or special care nursery.Hypoglycaemia.Neonatal jaundice.Blood glucose in first 6 weeks postpartum.Length of hospital stay.Hospital admissions in the first year of life.Mortality within the first year.

### Explanatory variables

Individual explanatory variables will include as follows:

Demographic and socioeconomic factors:Maternal age.Country of birth.Aboriginality.Residence remoteness, calculated using Statistical Area 2 of residence (SA2), the Australian Bureau of Statistics (ABS) remoteness classification for Statistical Area 1 and the population-weighted correspondence to SA2.Area-level socio-economic status (using the ABS Socio-Economic Indices for Areas classification for SA2).Maternal risk factors:Maternal height, weight and BMI.Previous birth outcomes.Parity.Smoking in pregnancy.History of endocrine, metabolic and gynaecological conditions.Chronic conditions and previous surgery.Pregnancy risk factors:Plurality.Gestational hypertension and pre-eclampsia.Assisted reproductive technology.Antenatally identified foetal growth restriction and macrosomia.Antenatal electrolytes and results of liver function tests, full blood count coagulation studies and urine tests.Antenatal medical treatment of GDM (insulin, oral hypoglycaemic medication).Health service use:Birth hospital.Antenatal care information.Model of care.Antenatal ED and hospital admissions.Labour and birth characteristics:Labour onset, induction and augmentation of labour.Labour interventions.Mode of birth.Pain relief.Gestational age.

### Analysis plan: risk prediction models (aim 1)

A K-fold approach will be used to derive and validate risk prediction models identifying groups of women with GDM who are at higher or lower risk of adverse outcomes. The study population, comprising all women in the cohort who have been identified as having GDM, will be randomly divided into roughly equal subgroups balancing prediction error and computational time. In each fold, one subgroup will be a validation cohort, and the other subgroups will be combined as the derivation cohort. Figure 3 provides an illustration of the k-fold approach using an 8-fold as an exemplar of the methodology, where the whole population gets randomly assigned to eight roughly equal groups. Once assigned, individuals remain in their allocated group. A ‘fold’ refers to a round of analysis where the remaining groups are combined to generate the risk prediction model while the validation cohort is then used to validate it. In an eightfold, these analyses are run eight times, with each group being used as the validation cohort once and as part of the derivation cohort seven times.

**Figure 3 F3:**
[figure not shown]
Derivation and validation cohorts for each of the eight folds.

Using the derivation cohort, univariate repeated measures logistic regression modelling will assess the relationship between the primary composite outcome (any of the following: large for gestational age, stillbirth, neonatal death, shoulder dystocia, bone fracture, arm/hand palsy related to birth injury, gestational hypertension or pre-eclampsia) and explanatory variables. Repeated measures logistic regression will take into account the non-independence of two or more pregnancies to the same woman during the study period. Two-way interactions (eg, BMI and hyperglycaemia) will be examined, and the collective and individual effect on the multivariate model assessed. Multivariable repeated measures logistic regression will estimate adjusted ORs and their 95% CIs.

Using the validation cohort, agreement between the predicted and observed probabilities of the primary composite outcome will be assessed by Hosmer-Lemeshow goodness of fit testing.^25^ Ability of the prediction model to differentiate high-risk and low-risk women will be assessed using area under the receiver operating characteristics curve.^26^ The sensitivity, specificity, negative and positive predictive values will be calculated for each validation cohort.

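### Aim 1's primary composite mixes overgrowth outcomes with perinatal death and has no small-baby or neonatal-morbidity component, so its lower-risk group can hide raised perinatal mortality

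*Protocol article*

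**What the plan says.** The aim 1 analysis section of the Protocol article sets out models for "identifying groups of women with GDM who are at higher or lower risk of adverse outcomes". The modelled outcome is a "primary composite outcome (any of the following" list made up of "large for gestational age, stillbirth, neonatal death, shoulder dystocia, bone fracture, arm/hand palsy related to birth injury, gestational hypertension or pre-eclampsia". Each component counts the same.

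The Outcome variables section places the two birth-size outcomes side by side, "Large for gestational age.Small for gestational age", and also lists a validated neonatal morbidity composite. Neither SGA nor that morbidity composite enters the aim 1 primary outcome.

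The aim 1 section relates the composite to the explanatory variables without saying which are eligible. The Explanatory variables section includes "Antenatally identified foetal growth restriction and macrosomia", smoking in pregnancy, and "Gestational hypertension and pre-eclampsia".

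In each validation cohort, Hosmer-Lemeshow testing is specified on the composite. The area under the curve, sensitivity, specificity and predictive values are described for the same model, with no other outcome named. The Introduction says that aim 1 results will let obstetricians target surveillance and intervention better. Ethics and dissemination mentions a possible risk tool for use in consultations.

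**The concern.** An any-of outcome is governed by its common components. Here those are likely to be LGA and hypertensive disorder; stillbirth and neonatal death are rare. The components need not move together. A predictor that marks a small baby makes LGA, shoulder dystocia and birth injury less likely, and may make perinatal death more likely. In a single model the fall in the common components can outweigh the rise in the rare fatal ones, so the predictor looks protective.

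Stillbirth and neonatal death are named in the composite, so a reader will take a lower-risk label to cover them. The planned calibration and discrimination checks cannot test that reading, because they ask only whether the composite is predicted well. A model that predicts LGA and hypertensive disorder well would validate well whatever it implied about death.

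The gap is wider than small babies. The Introduction attributes to maternal GDM an "increased risk of preterm birth, higher birth weights, admission to neonatal intensive care, hypoglycaemia, respiratory distress" in the children. Of these harms, only higher birth weight is represented in the composite.

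**Working it through.** The article states no event rates, sample size or power figure for aim 1, so there is no figure of the plan's own to reproduce. What follows is an illustration. Every component risk, including higher mortality with growth restriction, is an assumption, and components are treated as independent.

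**Formula.** Composite risk = 1 − (1 − LGA)(1 − hypertensive disorder)(1 − dystocia/injury)(1 − perinatal death).

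**Central case**

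| | LGA | Hypertensive disorder | Dystocia/injury | Death | Composite |
|---|---|---|---|---|---|
| Average woman with GDM | 12% | 8% | 3% | 0.5% | 1 − 0.88 × 0.92 × 0.97 × 0.995 = 21.9% |
| Growth-restricted, death tripled | 0.5% | 8% | 0.5% | 1.5% | 1 − 0.995 × 0.92 × 0.995 × 0.985 = 10.3% |
| Same, hypertensive disorder doubled | 0.5% | 16% | 0.5% | 1.5% | 1 − 0.995 × 0.84 × 0.995 × 0.985 = 18.1% |

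Deaths are 0.5/21.9, or about 2%, of the average woman's composite risk.

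**Death risk needed to rank as average.** Setting the growth-restricted composite equal to 21.9% and solving for death gives 1 − 0.7814/(0.995 × 0.92 × 0.995) = 14.2%. With doubled hypertensive disorder it is 1 − 0.7814/(0.995 × 0.84 × 0.995) = 6.0%.

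**Where the ordering reverses**
- Central case, solving for hypertensive disorder: 1 − 0.7814/(0.995 × 0.995 × 0.985) = 19.9%, and 19.9/8 is about 2.5 times. If tripled, the growth-restricted composite is 25.9% against 21.9%.
- Over LGA 8–18% and hypertensive disorder 5–10%, the ordering holds throughout if hypertensive disorder is unchanged or 1.5 times as common in growth restriction. At the least favourable corner (LGA 8%, hypertensive disorder 10%), 1.5 times gives 17.1% against 20.1%.
- If it is doubled, the ordering reverses in one corner of that range: LGA 8% with hypertensive disorder 9% (20.0% against 19.2%), and hypertensive disorder 10% with LGA 8%, 9% or 10% (22.0% against 20.1%, 21.0% and 21.8%).

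**Second set of assumptions.** LGA 12%, hypertensive disorder 8%, injury 2% and death 0.4% without growth restriction give 21.0%. With growth restriction, five-fold death (2%), and LGA and injury at 0.5% each, the composite is 10.7%, 14.6% or 18.5% for hypertension ratios of 1, 1.5 or 2. The break-even ratio is 2.3 here. It runs from 1.4 to 4.1 over LGA 8–16%, hypertensive disorder 5–12% and death ratios of 3 to 10.

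**If hypertensive disorder is itself a predictor.** Growth restriction is then judged conditional on it. Among women without it, the central inputs give 1 − 0.995 × 0.995 × 0.985 = 2.5% against 1 − 0.88 × 0.97 × 0.995 = 15.1%, so the counterweight disappears.

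**The case against.** **Growth restriction may not enter the model.** The explanatory list serves all three aims and includes items such as pain relief and mode of birth that could not serve an antenatal model. The Abstract frames aim 1 around women having glucose tolerance testing, and growth restriction identified later would be unknown then. This stands: growth restriction is a candidate, not a confirmed predictor. However, the aim 1 section sets no restriction. Smoking raises the same question and could be known early, though no figures are offered for it here.

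**The composite suits the disease.** Overgrowth, birth injury and hypertensive disorder are recognisable GDM outcomes, and the harms listed in the Introduction do not include small size. This also stands, so the article gives no ground for saying the primary outcome must be rebuilt. But the stated target is adverse outcomes in general, and that same list supports the point about neonatal morbidity.

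**Further models may sit in a fuller plan.** The section speaks of models in the plural, and a condensed article need not list every secondary analysis. Their absence is therefore not an omission to criticise. The point concerns what is fixed: this composite, validated as described, and the use intended for its risk groups.

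**The harm is limited.** The tool is only a possibility, meant as an added resource for shared decisions, and a clinician already knows of antenatally identified growth restriction. That lowers the stakes but does not make the label accurate.

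**Conclusion.** The concern holds as a possibility that the planned validation cannot exclude. Under the central assumptions a growth-restricted pregnancy with tripled death risk scores 10.3% to 18.1%, against 21.9% for the average woman.

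A reader might infer that the model is bound to give growth restriction a protective coefficient, or that the ordering holds across all plausible rates. The documents support neither. They give no component rates, the link between growth restriction and death is an outside premise, independence is assumed, and the ordering reverses when hypertensive disorder is sufficiently more common in growth restriction.

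A reader might also infer that the primary model should be limited to singletons, or that a woman should count as lower risk only if she is low on every component. These are preferences that nothing in the article requires; plurality is already a listed explanatory variable.

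**What to change.** Keep the composite as the primary outcome, and add the following:

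1. In the same folds, fit and validate component-level models for (a) LGA, shoulder dystocia or birth injury; (b) hypertensive disorder; (c) perinatal death or SGA; and (d) the validated neonatal morbidity composite.
2. Report observed perinatal death, SGA and neonatal morbidity by predicted-risk group of the composite model.
3. Describe the composite's lower-risk group as low risk for those outcomes only if these results support it.

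All the outcomes are already listed and the data are already to be linked. The cost is a few extra models and tables. Estimates for death will be imprecise and should be shown with their intervals.
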